## Abstract

**Background:**

Current guidelines for the management of patients with specific low back pain pathology suggest non-surgical intervention as first-line treatment, but there is insufficient evidence to make recommendations of the content in the non-surgical intervention. Opinions regarding the dose of non-surgical intervention that should be trialled prior to decision making about surgery intervention vary. The aim of the present study is to investigate if physiotherapy administrated before surgery improves function, pain and health in patients with degenerative lumbar spine disorder scheduled for surgery. The patients are followed over two years. A secondary aim is to study what factors predict short and long term outcomes.

**Methods:**

This study is a single blinded, 2-arm, randomized controlled trial with follow-up after the completion of pre-surgery intervention as well as 3, 12 and 24 months post-surgery. The study will recruit men and women, 25 to 80 years of age, scheduled for surgery due to; disc herniation, spinal stenosis, spondylolisthesis or degenerative disc disease. A total of 202 patients will be randomly allocated to a pre-surgery physiotherapy intervention or a waiting list group for 9 weeks. The waiting-list group will receive standardized information about surgery, post-surgical rehabilitation and advice to stay active. The pre-surgery physiotherapy group will receive physiotherapy 2 times per week, consisting of a stratified classification treatment, based on assessment findings. One of the following treatments will be selected; a) Specific exercises and mobilization, b) Motor control exercises or c) Traction. The pre-surgery physiotherapy group will also be prescribed a tailor-made general supervised exercise program. The physiotherapist will use a behavioral approach aimed at reducing patient fear avoidance and increasing activity levels. They will also receive standardized information about surgery, post-surgical rehabilitation and advice to stay active. Primary outcome measure is Oswestry Disability Index. Secondary outcome measures are the visual analogue scale for back and leg pain, pain drawing, health related quality of life, Hospital anxiety and depression scale, Fear avoidance beliefs questionnaire, Self-efficacy scale and Work Ability Index.

**Discussion:**

The study findings will help improve the treatment of patients with degenerative lumbar spine disorder scheduled for surgery.

**Trial registration:**

ClinicalTrials.gov reference: NCT02454400 (Trial registration date: August 31st 2015) and has been registered on ClinicalTrials.gov, identifier: NCT02454400.

## Background

Low back pain (LBP) have a lifetime prevalence to up to 84 % and is a major cause of disability with substantial socioeconomic impact globally [1]. The highest prevalence is in age-group 45–64 and many experience functional impairments and activity limitations. Up to 85 % of LBP is considered to have non-specific etiology [2] when the mechanism for LBP cannot be clearly identified. LBP can be the product of nociception from lumbar spine structures [3] or even the result of centrally mediated pain in the absence of nociception [4]. Different LBP related pathologies can coexist but approximately 5 % of those receive a primary diagnosis of disc herniation [5], 3–4 % spinal stenosis [6] and lower number with spondylolisthesis and degenerative disc disease (DDD). In Swedish Spine register of spinal surgery patients these diagnoses are concluded as degenerative lumbar spine disorders [7].

Guidelines published internationally focusing on the management of LBP in primary care recommend screening for serious pathology, neurological symptoms, the consideration of psychosocial risk factors if there is no improvement and to avoid routine imaging for non-specific LBP [8]. The prevalence of serious pathology in the form of malignancy, spinal fracture, infection, or cauda equine syndrome requiring referral to secondary or tertiary medical care occurs in only <1–4 % of primary health care LBP cases [9–11]. Guidelines recommend a multicomponent strategy for patients with longstanding LBP including supervised exercises and behavioral approach based on the presence of yellow flags [8].

Consistencies in the patient’s history, physical assessment, clinical tests and medical imaging may strengthen suspicion of specific pathologies such as disc-herniation, spinal stenosis, spondylolisthesis and DDD causing LBP [12–15]. In the absence of serious pathology, disc herniation usually has a good prognosis and non-surgical intervention is recommended 8–12 weeks before decision-making about surgery [16–18]. Leg pain intensity is a significant prognostic factor for subsequent surgery after non-surgical intervention [14]. A recent overview of the literature suggests that surgery leads to short-term benefits for leg pain and to a lesser extent for LBP when compared with non-surgical treatment. Despite this, no short-term and long term effects have been observed for functional outcome measures [5]. It is also uncertain if surgical intervention has positive or negative effects on the underlying disc disease in a longer perspective [5]. In disc herniation, similar results have been observed for non-surgical and surgical intervention at one [5, 18] and two years follow-up [5], which supports the view that the non-surgical intervention should be thoroughly tested before decision making about surgery.

In mild to moderately symptomatic degenerative lumbar stenosis, the prognosis can be favorable in up to half of patients and non-surgical intervention is recommended before decision-making about surgery [19]. However, a recent Cochrane review suggests that, high quality studies are needed to inform future evidence based guidelines about the content of the non-surgical intervention [20]. The prevalence of spinal stenosis is increasing and therefore high quality research its management is of importance [20]. In the older population spinal stenosis is the most common reason for spinal surgery. Surgical intervention is recommended in moderate to severe spinal stenosis [19], but up to 35 % of the patients remain doubtful or dissatisfied with the result of surgery [7].

Current guidelines for the management of degenerative lumbar spondylolisthesis suggest that when there is a predominance of stenotic radicular symptoms, treatment should be similar to treatment for symptomatic degenerative lumbar spinal stenosis [21]. Therefore, surgical intervention is recommended when symptomatic spinal stenosis associated with low grade degenerative lumbar spondylolisthesis is recalcitrant to trial of non-surgical intervention [20]. There is currently a limited evidence base comparing the two interventions for spondylolisthesis suggesting surgical intervention to be more successful than non-surgical intervention for pain and functional outcomes [22].

In patients with DDD, both non-surgical and surgical interventions have limited evidence [18]. In a review of systematic reviews and RCTs, Jacobs et al [18] reported that for DDD, surgery is no more effective than high-intensity non-surgical interventions for improvements in pain scores or function. Similarly, a recent systematic review and meta-analysis suggests that there is strong evidence that lumbar fusion surgery is not more effective than non-surgical interventions in reducing disability because of chronic LBP [23].

Previous literature on the treatment of LBP has often been based on generic treatments for patients with heterogeneous body functional impairments and activity limitations. This may explain the small effect sizes reported in clinical trials [24]. Recently attention has shifted to the homogenous classification of patients based on functional impairments and activity limitations with the aim of improving the effectiveness of individualized treatments [25]. This has led to a focus on stratified care for LBP in the area of physiotherapy [25]. One of these stratification care models is the Treatment Based Classification (TBC), using criteria from the subjective and physical assessment to classify patients to different treatment classifications [26]. TBC has shown better treatment outcome than treatment according to guidelines in acute LBP [27], but this effect has not been found in patients with long-lasting non-specific LBP [28].

High quality evidence-based guidelines for the non-surgical intervention of these degenerative lumbar spine disorders are lacking. The optimal duration of non-surgical intervention before surgical intervention is considered unclear. For those patients selected for surgical intervention, there is currently a small body of literature suggesting that pre-surgery physiotherapy improves the outcome of spinal surgery [29, 30]. Nielsen et al showed that supervised home exercise to improve trunk muscle strength and cardiovascular conditioning gave better post-operatively functionality, faster recovery and shorter hospital stay. The patients reported higher level of satisfaction in the intervention group [29]. Louw et al tested the effect of pre-surgery education, which showed lower health care consumption and a more favorable surgical experience [30]. No study has tested a more comprehensive exercise program pre-surgery. In hip pathology, physiotherapy prior to joint replacement surgery has been shown to reduce pain and improve physical function in preparation for surgery [31]. The extent to which patients have access to non-surgical intervention prior to decision-making about surgery is also lacking in the literature. Only 10 % of the clinical studies about the effect of surgery have information about non-surgical intervention prior to surgery for spinal stenosis [32]. We hypothesize that supervised exercises that have been proposed for non-specific LBP combined with a TBC could be effective also for patients awaiting elective surgery. The prognosis of LBP is multifactorial and therefore it is of interest to understand other factors apart from pre-habilitation that can influence short- and long term outcome.

### Objectives

The aim is to investigate if physiotherapy administrated before surgery improves function, pain and health in patients with degenerative lumbar spine disorder scheduled for surgery. The patients are followed over two years. A secondary aim is to study what factors predict short and long term outcomes.

### Trail design

This study protocol describes a single blinded, 2-arm, randomized controlled trial with 2 year follow up and the 1 year follow up as primary end point. The protocol conforms to the SPIRIT 2013 recommendations.

## Methods

### Study setting

A total of 202 consecutively selected patients will be included in the study. All patients are referred to the Spine Clinic at the University Hospital in Linkoping, Sweden. Individuals that fulfil the inclusion criteria will be asked to participate. After signed informed consent has been obtained, baseline measurement will be collected and randomisation will take place.

### Eligibility criteria

Inclusion criteria; Males and females aged 25–80 years that are scheduled for surgery with degenerative lumbar spine disorder; presence of low back and/or leg pain due to disc herniation, spinal stenosis, spondylolisthesis (Grade 4), degenerative disc disease (DDD); diagnosis confirmed by magnetic resonance imaging; pain level high enough to indicate surgical intervention; fluent in Swedish.

Exclusion criteria: Patients that are in need of acute surgery; have severe spinal pathology (such as osteoporosis, or fusion > 4 levels (5 vertebras) or other severe diagnoses; patients in need of re-surgery on the same level.

### Interventions

#### Pre-surgery waiting list group

Patients will receive standardized information about surgery from an orthopedic surgeon, post-surgery rehabilitation and advice to stay active.

#### Pre-surgery physiotherapy group

Patients will receive pre-surgery physiotherapy intervention twice a week for 9 weeks. The program is multicomponent and will include:Active physiotherapy according to a TBC; a) Specific exercises and mobilization, or b) Motor control exercises or c) Traction.Tailor-made general supervised exercise program.Behavioral approach to reduce fear avoidance and increase activity level.

Patients will also receive standardized information about surgery from an orthopedic surgeon, post-surgery rehabilitation and advice to stay active.

The physiotherapy intervention will be performed at one of eleven different physiotherapy clinics in Östergötlands county, close to the patient’s home. The physiotherapists delivering the intervention program will be trained by two specialist physiotherapists with two initial meetings and three follow ups during the study. For each patient the physiotherapist will follow a checklist with treatment and progression planned for each treatment-session, but modified to suit the patient. The content in the exercise-program will include 10 min intervals of cardiovascular-exercise in the beginning, in the middle and at the end of each session. Further it will include 5–6 exercises based on the patients’ function, posture and PSFS (patient specific functional scale) with the dosage of 15 repetitions in three sets. Variation of exercise equipment and consideration of the need of different starting positions is recommended and if possible the prescription of some exercises in upright standing. At least one exercise will be altered every third visit, both with aim of progressing the training as well as providing a distractive pain coping strategy. The Borg scale [33] will be used for rating the perceived exertion of each exercise session. The prescribed level of exertion for each exercise session will be 12–13 on Borg Scale. If the patient score lower than 12–13 on the Borg scale, the patient will be informed to increase the intensity of the exercises. The patients will also receive written and illustrated descriptions of exercises and their dosage in the exercise-program. At home, the patients will complete a logbook of self-mediated home exercise and general physical activities. A treatment demarcation table will be provided outlining the intervention content for each group (Table 1). Checklists and logbooks will provide data regarding adherence. The physiotherapist will urge the patients to continue the treatment program and the reason for terminating will be noted. A minimum intervention quota of 50 % will be required to be fulfilled for the intervention to be considered as compliant. Spinal surgery and post-surgery rehabilitation will be performed according to clinical routine [5].

**Table 1 Tab1:** Components of the two intervention protocol used in the trial

Treatment components	Waiting list group	Pre-surgery physiotherapy group
1a. Specific movement and mobilisation - Mechanical loading strategies; repeated movements according to directional preference, mobilisation, and integration in a functional restoration program.	**X**	**TBC**
1b. Motor control exercise - Exercise focused on trunk and pelvic floor muscle activation and integration in a functional restoration program	**X**	**TBC**
1c. Traction - Manual Traction producing symptom reduction	X	**TBC**
2. Tailor-made general supervised exercise program - Individualised prescription (type of exercise and load) of aerobic, resistance, flexibility exercises with information documents and checklist for treatment, progression and dosage	X	**✓**
3. Behavioral approach: - Goal setting (establishment and regular reviews) - Strategies to minimize barriers to goal attainment, for example education regarding; ergonomics, postural alignment, patho-anatomical/physiological explanation - Self-mediated home exercise and physical activities (logbook)	X	**✓**
Advice regarding general physical activity recommendations	**✓**	**✓**
Education regarding surgery	**✓**	**✓**
Education regarding post-surgical rehabilitation	**✓**	**✓**
Pre-surgical re-evaluation	**✓**	**✓**

Spinal surgery and post-surgery rehabilitation in both groups is performed according to existing clinical routine [5]

✓ component mandatory, ***X*** component not allowed, ***TBC*** treatment based classification component with modifications

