### Sample size

Based on a minimally clinical important change of 10 % on the ODI [45], a standard deviation for the ODI =20, a significance level of *p* = 0.05, a power of 80 %, an estimated 64 patients are required in each of the intervention groups, at the primary endpoint. The current sample size of 202 patients allows for a 35 % loss to follow-up while maintaining >80 % statistical power.

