### Statistical methods

Data collected at the longitudinal time points will be analysed according to the ‘intention to treat’ (ITT) principle. Data analysis according to ITT requires that data for every patient, regardless of level of intervention compliance, data missing at follow-up or due to drop-out, will be included in the group to which they are randomised [50]. To perform an ITT analysis, missing data will be replaced through multiple imputation methods. In an attempt to determine the sensitivity of the ITT data, it will be compared to per-protocol data from patients who have complied with the original study protocol. Alternative analyses will also be performed to take treatment compliance into consideration. Analysis of variance ANOVA will be used to investigate within and between group differences in longitudinal outcome measures. Within and between group Cohens *d* effect sizes will also be calculated. Multivariate regression will be used to analyse potential predictors of long term outcomes.

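### The sample size makes no allowance for clinic clustering in the physiotherapy arm, so the roughly 1-point power margin at 35% loss disappears once the clinic ICC exceeds about 0.01 to 0.02

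*Protocol article*

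**What the plan says.** Under the heading Pre-surgery physiotherapy group, the protocol article says that "The physiotherapy intervention will be performed at one of eleven different physiotherapy clinics", chosen to be near the patient's home. Table 1 marks the classification-based treatments, the supervised exercise program and the behavioral approach as not allowed in the waiting-list group. Treatment delivery is therefore nested in clinics in one arm and not in the other.

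The Sample size section rests on a "minimally clinical important change of 10 % on the ODI", "a standard deviation for the ODI =20", "a significance level of *p* = 0.05" and 80% power. It concludes that "an estimated 64 patients are required in each of the intervention groups, at the primary endpoint", and adds: "The current sample size of 202 patients allows for a 35 % loss to follow-up while maintaining >80 % statistical power". It mentions neither clinics nor a design effect.

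The Statistical methods section says: "Analysis of variance ANOVA will be used to investigate within and between group differences in longitudinal outcome measures". No clinic or therapist term is mentioned. The Trial design section makes the 1-year follow-up the primary endpoint.

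**The concern.** The program depends on who delivers it: exercises are prescribed and progressed individually, goals are set and reviewed, and fear avoidance is addressed by the treating physiotherapist. Patients treated at the same clinic may therefore have correlated outcomes. If so, the mean of the physiotherapy arm varies more than it would for the same number of independent patients, while the waiting-list mean is unaffected. This is a partially nested design.

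Two separate consequences are at stake:

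- **Power.** A test that uses the correct, larger standard error has less power than the Sample size section states. That statement has little room to absorb a loss.
- **Type I error.** If the ANOVA ignores clinic, its standard error is too small whenever the ICC is positive, and the error rate exceeds the nominal 5%.

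**Working it through.** **Inputs.** From the protocol article: difference 10, SD 20, alpha 0.05 (taken as two-sided, which reproduces the stated figure), power 80%, 202 patients allocated 1:1, 35% loss, 11 clinics in one arm. Assumed, because the documents do not give them: ICC from 0.01 to 0.10, total SD held at 20, and equal clinic sizes unless stated.

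**Step 1: reproduce the stated figures.** The normal approximation gives 2 × (1.96 + 0.842)² × 20² / 10² = 62.8, so 63 per arm. The two-sample t-test gives 63.77, so 64 per arm, as stated. After 35% loss, 202 × 0.65 = 131.3, or 65.65 per arm. The t-test then has power 81.1% (80.8% at 65 per arm). The claim of more than 80% holds under independence, by about one point.

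**Step 2: add clustering in the physiotherapy arm.** Patients per clinic: m = 65.65 / 11 = 5.97. Design effect in that arm: DE = 1 + (m − 1) × ICC. Standard error of the difference: 20 × √[(DE + 1) / 65.65]. Power A uses the noncentral t with 2n − 2 degrees of freedom. Power B uses Satterthwaite degrees of freedom, with 10 for the clinic-based component.

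| ICC | DE | SE relative to independence | Power A | Power B |
|---|---|---|---|---|
| 0 | 1.000 | 1.000 | 81.1% | – |
| 0.01 | 1.050 | 1.012 | 80.2% | 78.5% |
| 0.02 | 1.099 | 1.025 | 79.3% | 77.4% |
| 0.05 | 1.248 | 1.060 | 76.5% | 74.3% |
| 0.10 | 1.497 | 1.117 | 72.1% | 69.4% |

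The ICC at which power reaches 80% is 0.012 on basis A. By normal approximation it is 0.018, or 0.014 if 65 per arm is used. On basis B, power is already below 80% at ICC 0.01.

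Unequal clinic sizes make this worse. With an assumed coefficient of variation of 0.6, DE = 1 + (1.36 × m − 1) × ICC, and power on basis A is 78.4% at ICC 0.02 and 74.5% at 0.05.

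**Step 3: full follow-up.** With 101 per arm, m = 9.18. Power by normal approximation is 93.6%, 92.7%, 89.9% and 84.9% at ICC 0.01, 0.02, 0.05 and 0.10. With Satterthwaite degrees of freedom it is 92.3%, 91.2%, 87.8% and 81.8%.

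**Step 4: how much loss is tolerable.** By normal approximation, 80% power needs 72 analysed per arm at ICC 0.05 and 84 at ICC 0.10. The tolerable loss is then 1 − 72/101 = 28.7% and 1 − 84/101 = 16.8%, rather than 35%.

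**Step 5: type I error of an ANOVA that ignores clinic.** With clinic effects random, this is 2 × [1 − Φ(1.96 / r)], where r is the SE ratio. At 35% loss it is 5.3%, 5.6%, 6.5% and 7.9% across the four ICC values. With full follow-up it is 5.5%, 6.0%, 7.4% and 9.9%.

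**The case against.** The strongest reply is that everything here depends on an ICC that the documents do not give, and that it may be small. Patients come from one spine clinic and are individually randomised. The treating physiotherapists share training and work from a session checklist, and the treatment class is assigned by a blinded assessor. The primary endpoint is one year, after surgery and rehabilitation that follow the same routine in both arms. Tailoring to the patient is not in itself evidence of similarity within a clinic. This stands. A reader might infer that the claim of more than 80% power is simply false, or that the standard errors are certainly too small. The documents support neither: at ICC 0.01 power is still 80.2% on basis A.

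A second reply is that the Statistical methods section is a short article summary. It names ANOVA but does not say that clinic will be ignored, and an analysis plan that is not shown may include a clinic term. This also stands, so the type I error figures are conditional. It does not answer the power point: a clinic term would make the standard error valid but would not restore the margin stated under Sample size.

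Third, a reader might add the power loss to the type I error inflation. They belong to different tests. At 65 per arm, the unadjusted test would reject in 81.1%, 80.8%, 80.0% and 78.8% of trials under the alternative at the four ICC values, so up to ICC 0.05 its problem is error rate and not power. The inflation also depends on treating clinics as random. It does not arise through treatment delivery if inference is confined to these eleven clinics, or if physiotherapy has no effect in any of them.

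Finally, adjustment for baseline ODI could offset the power loss, but only by an amount that depends on the baseline-outcome correlation ρ, which the documents do not give. Assuming that adjustment multiplies the whole variance by 1 − ρ², at 65 per arm by normal approximation 80% power needs a standard error of 10 / 2.802, a variance of 12.74. At ICC 0.05 the variance is 13.82, so ρ = √(1 − 12.74/13.82) = 0.28. At ICC 0.10 the variance is 15.33 and ρ = 0.41.

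**Conclusion.** The point holds in conditional form. Delivery is nested in eleven clinics in one arm, the sample size treats all patients as independent, and the power statement at maximum loss has a margin of about one point. That margin is lost once the clinic ICC exceeds about 0.01 to 0.02, and sooner with small-sample degrees of freedom or unequal clinic sizes.

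The effect is modest. For ICC 0.01 to 0.05 it costs about 1 to 5 points of power on basis A, and power falls below 80% only near the maximum 35% loss; with full follow-up it stays above 80% across the assumed range with equal clinic sizes. There is no arithmetic error in the Sample size section. The conclusion rests on the assumed ICC range, a total SD of 20 and, in the main table, equal clinic sizes. Clustering by individual physiotherapist cannot be sized, because the number of physiotherapists is not given.

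**What to change.** - Fit the primary ODI comparison with a random clinic effect in the physiotherapy arm only, using small-sample degrees of freedom. At the least, prespecify this as a sensitivity analysis to the ANOVA.
- Restate the power sentence as holding only under negligible clinic clustering, or give power over a stated ICC range at 35% loss and at full follow-up.
- If baseline ODI adjustment is offered as compensation, state the baseline-outcome correlation that is assumed.

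The cost is one variance term, a slightly wider confidence interval and a slightly less favourable power statement. No extra patients and no design change are needed.
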